### Target group, inclusion and exclusion criteria

The study will include patients (male and female of the age of 18 or older) who, according to the judgment of the practicing neurologist, have a suspected or manifest disease giving rise to the medical indication to record an EEG (first or repeated) within the framework of usual statutory care (i.e., billing numbers EBM 16310 or 16311). The private practitioner will be responsible for the selection and the information of the patients.

In both study phases, patients who have to be treated after the first EEG due to hazard prevention will not be included in the study. In addition, patients under the age of 18 will be excluded.

### Patient information and consent

The private practitioners in charge will explain the objectives of the study and the process by which it will be performed to the patients before asking them to sign a consent form in which they agree to the following: portable EEG monitoring, diagnostic second opinion by the University Department of Neurology Magdeburg, data evaluation, and data storage. The signed consent form will remain with the private practitioner. In the event of a possible revocation, the physician shall immediately inform the university department.

### Indication, implementation, and evaluation of EEGs

Before using the conventional EEG, the private practitioner will document the diagnostic question and the therapeutic options. This will serve as the proof for the indication of the conventional EEG. The private practitioner will also document the patient’s medical history.

Both the conventional practice EEG and the portable EEG will be derived in the pilot study phase (first phase) according to uniform standards over 20 min as per the German Society of Clinical Neurophysiology (DGKN) guidelines [13].

In the feasibility study phase (second phase), the EEGs will be derived according to the guidelines of the German Society of Clinical Neurophysiology (DGKN) [13, 14] per the neurologist (possibly also as long-term EEG). The portable EEG will be stored on a memory card that is integrated into the headset. The patients will return with the headset and activity and evaluation sheet, which they will be required to complete.

Subsequently, in both phases of the HOME^ONE^ study, the private practitioner will examine both EEGs using the same standardized assessment sheet.

Both results will be collected by a staff member of KNEU. In the run-up to the second assessment of both EEGs, the Data Trustee will transfer the data from the conventional EEG devices into the standardized format of the portable EEG device and will blind all EEGs. The blinded EEGs will then be examined by two experienced neurologists from KNEU.

### Data analysis and measures

Comparing the two EEG recording methods, the conventional practice EEG cannot be the gold standard to determine the sensitivity, specificity, and predictive values of the portable EEG. The goal that underpins the use of the portable EEG is to gain additional diagnostic insights through extended use. However, in the present state of the method, the portable EEG can remain behind the conventional practice EEG in its diagnostic yield, for example, due to increased artifacts or errors in handling by the patient. As such, it will be necessary to document the technical assessment and the extent to which there is concordance between the two EEGs.

In the pilot study phase, all three assessors will evaluate the technical quality of the EEG records according to the following ratings:The EEG record is unrestrictedly for medical reporting,The use of the EEG record for medical reporting is limited, andThe EEG record is not usable for medical reporting.

The evaluation of the technical quality is based on different criteria:The assessor’s overall impression on the EEG record,The frequency of artifacts,Strength of 50 Hz line noise, andRecovery of EEG traces after strong artifacts.

These criteria meet the standards of the International Federation of Clinical Neurophysiology (IFCN) for digital recording of clinical EEG [15].

In addition, all three assessors will document their medical reports for each blinded EEG record. After re-identification of the EEGs and the associated medical reports by the Data Trustee, the concordance (or discordance) will be evaluated. As measurements, we will use concordance rates and kappa values.

In the feasibility study phase, we will use the same approach. However, we will extend it as follows: To share information regarding a possible change of management, the private practitioner will classify the results of the conventional practice EEG according to the possibilities presented in Table 1.

**Table 1 Tab1:** Action-oriented classification of the findings of the conventional practice EEGs

1A	No action or follow-up appointment only
1B	Targeted referral for further clarification or co-treatment or further treatment
1C	Initiate or change therapy (adjust, switch, settle)

In the same way, they will also classify the results of the portable EEG (see Table 2).

**Table 2 Tab2:** Action-oriented classification of the results of the portable EEG

2A	No action or follow-up appointment only
2B	Targeted referral for further clarification or co-treatment or further treatment^a^
2C	Initiate or change therapy (adjust, switch, settle)

^a^If clarification or therapeutic clarity can only be established by targeted referral, this clarification is part of the contractual medical care, not the study

In a first simplified evaluation level, the combinations (1A and 2A) as well as ((1B or 1C) will be (2B or 2C)) concordant. This results in Table 3.

**Table 3 Tab3:** Test assessment of conventional and portable EEGs by the private practitioner

Practice EEG	Portable EEG		Total
	Action (2B, 2C)	No action (2A)	
Action (1B, 1C)	a	b	a + b
No action(1A)	c	d	c + d
Total	a + c	b + d	a + b + c + d

This represents an intra-individual method comparison with a binary result criterion (“change of management”): The case management sequences of the portable EEGs are the same as those of the conventional practice EEGs (a or d), they are beyond (c) or remain behind (b). No decision should be made at this level (c) being “better” than (b).

To develop patients’ acceptability, we will use a questionnaire to measure relevant factors.

In an extended evaluation level, the results of the portable EEG will be more differentiated by means of the possibilities shown in Table 4.

**Table 4 Tab4:** Differentiation possibilities of the portable EEG results in an extended evaluation level

2A	No action or follow-up appointment only
2B1	Referral to the same specialist as 1B
2B2	Referral to a specialist different than 1B
2C1	Same therapeutic decision as 1C
2C2	Other therapeutic decision than 1C

The combinations of 1A with 2A are concordant with 1B with 2B1 and 1C with 2C1. The other combinations are discordant. Since the expected number of discordances is higher than the previous simplified classification, more cases than stated above will be required.

In the second part of the documentation, the attending physicians will document their gain in case management through the additional portable EEG and determine their disposition for their patient. In doing so, they will decide for themselves which of the possibly discordant EEG findings they consider superior. Since they know both findings and the patient, their two EEG assessments are not independent of each other.

The result of the second opinion in KNEU is subsequently included for the method comparison.

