### Objectives of the *HOME* project and specific objectives of the HOME^ONE^ study

The goal of the *HOME* project is to implement an EEG home-monitoring system with a patient-controlled portable dry electrode EEG recorder for use within the routine care of outpatients (for diagnostic purposes as well as for therapeutic management). The HOME^ONE^ study will be a two-phase (pilot study phase and feasibility study phase) intra-individual comparison that is driven by the following aims:To evaluate the technical usability and efficacy of the new portable dry electrode EEG recorder in comparison to the conventional EEG devices (pilot study phase);

To determine whether the pilot study objectives are met, we will analyze the technical assessments and EEG record examinations of the private practitioners and two experienced neurologists (percent of concordant readings and kappa values). After the technical usability and efficacy are shown, the second HOME^ONE^ study phase will be conducted. This feasibility study will aim to:(2)Assess patients’ acceptability and the feasibility of the EEG home-monitoring (feasibility study phase);(3)Provide insights into the extent of expectable diagnostic and therapeutic yields (feasibility study phase).

To evaluate whether this feasibility study was successful, we will analyze the before and after documented diagnostic findings and the therapeutic consequences of the private practitioners and compare them with those of two experienced neurologists. As is the case in the pilot study phase, a technical assessment is also part of the analyses.

If the two phases of the HOME^ONE^ study provide sufficient justification for technical usability, practical feasibility, and diagnostic and therapeutic yields, this will justify (indication-specific) full-scale randomized controlled trials or observational studies.

To realize the goals of the *HOME* project (and the HOME^ONE^ study), which is being performed by the University Department of Neurology Magdeburg, we established a network of practices of neurologists in Saxony-Anhalt, a federal state of Germany.

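### The pilot plan says all three assessors report on blinded EEGs, but the practitioner reads both EEGs before blinding takes place

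*Protocol article*

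**What the plan says.** The Protocol article describes the pilot readings in two places.

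- *Data analysis and measures*, on the medical reports: "In addition, all three assessors will document their medical reports for each blinded EEG record". The Data Trustee then re-identifies the records, and concordance rates and kappa values are computed. The three assessors are the private practitioner and the two KNEU neurologists.
- *Indication, implementation, and evaluation of EEGs*, for both phases: "the private practitioner will examine both EEGs using the same standardized assessment sheet". Next, "Both results will be collected by a staff member of KNEU". Blinding follows: "In the run-up to the second assessment of both EEGs, the Data Trustee will transfer the data from the conventional EEG devices" into the portable device's format and blinds all EEGs. Finally, "The blinded EEGs will then be examined by two experienced neurologists from KNEU".

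The section on the objectives makes these readings the evidence for the pilot: "we will analyze the technical assessments and EEG record examinations of the private practitioners and two experienced neurologists (percent of concordant readings and kappa values").

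**The concern.** Who was blinded determines what a concordance figure means. The pilot asks whether the dry-electrode cap gives the same findings as the conventional EEG. A reader who knows the patient and has both recordings may let the report on one shape the report on the other, which would raise agreement between devices for reasons unrelated to the cap. Agreement between raters is affected as well: an informed practitioner and a masked KNEU reader can differ because of what they know, not only because of how they read. If all three sets of reports are described as blinded, readers of the results cannot tell which figures are protected against this and which are not.

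**Working it through.** **Passages side by side**

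| Question | *Data analysis and measures* (pilot) | Rest of the article |
|---|---|---|
| Who reports on blinded records? | All three assessors | The two KNEU neurologists (*Indication, implementation, and evaluation of EEGs*) |
| When are records blinded? | Before all three reports, by implication | After the practitioner's examination and the collection of results (same section) |
| To which step is masking attached? | All medical reports | The second assessment at KNEU (*Randomized second assessment by KNEU*, including the Fig. 1 caption; *Privacy and ethics*) |

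1. No section describes a blinded reading by the practitioner.
2. In *Study phases and settings*, both pilot recordings are made in the practice during one consultation. The practitioner has already documented the diagnostic question and the history. Nothing conceals the patient from this reader, and no step before the reading conceals the device.
3. The practitioner also reads before the conventional recording is converted to the portable format. The KNEU readers read after it.
4. Later in *Data analysis and measures*, in the feasibility-phase text, the article accepts that practitioners know the patient and both findings, so that their two assessments are not independent. This applies to the pilot by analogy. The direct evidence for the pilot is the reading sequence, which is given for both phases.
5. Three assessors form three pairs. Practitioner with the first KNEU reader and practitioner with the second are mixed (informed against masked). Only KNEU with KNEU is masked on both sides.

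**The plan's own figure.** The pilot sample size uses a difference of 0.3 between overall and chance agreement and a relative error of 0.3: n = 1/(0.3² × 0.3²) = 1/0.0081 = 123.46, which matches the stated 123. It does not depend on blinding and is not in dispute.

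**Can the bias be sized?** Suppose the practitioner repeats the first report in a share q of patients, with chance agreement held fixed. Observed agreement Pa becomes Pa + q(1 − Pa), so kappa rises by q(1 − Pa)/(1 − Pe) = q(1 − kappa). The article gives neither q nor a between-device agreement level. The 0.3 above was set for agreement between raters, and it fixes only a difference, not kappa. Borrowing it with assumed splits:

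| Assumed Pa / Pe | Kappa | Rise at q = 0.25 | Rise at q = 0.50 |
|---|---|---|---|
| 0.9 / 0.6 | 0.3/0.4 = 0.75 | 0.06 | 0.13 |
| 0.8 / 0.5 | 0.3/0.5 = 0.60 | 0.10 | 0.20 |
| 0.6 / 0.3 | 0.3/0.7 = 0.43 | 0.14 | 0.29 |

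For scale, at Pa = 0.8, Pe = 0.5 and n = 130 the approximate standard error of kappa is √(0.8 × 0.2/130)/0.5 = 0.07. The range shows that the answer is set by the assumptions, so no single figure should be quoted.

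**The case against.** The strongest reply is that this is one loose word set against an otherwise consistent process. Every other description attaches masking to the KNEU step, and the article openly concedes the practitioners' non-independence in the second phase. On that view the sentence is a drafting slip, perhaps meaning records that are blinded at a later stage. This is plausible, and it lowers the seriousness. It does not remove the point: under the looser reading, the pilot measures still include unblinded practitioner readings, and the sentence still tells the reader otherwise.

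The reply also limits what may be inferred:

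- A reader might conclude that the technical-quality rating is falsely called blinded too. It is not. The sentence on technical quality does not mention blinding. That the practitioner rates quality without masking is a limitation, not a contradiction.
- A reader might assume a single kappa averaged over three assessors. No section says so; the objectives only list whose readings are analysed. For the feasibility-phase action classes, *Randomized second assessment by KNEU* lists practitioner and KNEU results as separate criteria.
- A reader might assume that the practitioner reads the two records together. The article gives no order or timing for the two readings.
- Practitioners are the routine users of the device, and the objectives name their assessments as evidence. Excluding them from the decision to start the second phase would conflict with that section and is not needed to resolve this point.

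**Conclusion.** The point stands as an internal contradiction about blinding, with a consequence for how the pilot results are read. As written, the practitioner's medical reports cannot be blinded. The practitioner's between-device concordance is unblinded and may be biased upward, and practitioner-versus-KNEU kappas compare an informed reading with a masked one. Only agreement between the two KNEU readers is masked on both sides. The article does not define what is masked (device, patient or pairing), and it uses pseudonymisation for the same KNEU step.

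The size of any bias cannot be derived from the documents; the kappa shifts above are illustrations. It is tempting to conclude that the feasibility phase would be released on an artefact. The article makes that phase follow once usability and efficacy are shown, but the section on the objectives states no kappa threshold, so an effect on that decision cannot be demonstrated. The matter is worth correcting, but it does not invalidate the pilot.

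**What to change.** 1. In *Data analysis and measures*, limit the statement on blinded medical reports to the two KNEU assessors. If a blinded practitioner reading is intended, describe that step in *Indication, implementation, and evaluation of EEGs*.
2. Take the blinded KNEU readings as the main pilot result for concordance and kappa between conventional and portable EEG.
3. Report the practitioner's between-device concordance and technical ratings separately, labelled unblinded.
4. Report practitioner-versus-KNEU and KNEU-versus-KNEU agreement separately for each EEG type.
5. Practitioner assessments can remain part of the usability evidence named in the objectives.

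If the statement is limited to KNEU, the cost is a change of wording and a split of results already planned, with no extra readings. The main between-device result would rest on two readers instead of three and may look less favourable. Adding a blinded practitioner reading would instead require a further reading step.

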**Fig. 1 Fig1:**
[figure not shown]
Process sequence of data management, blinded second assessment (KNEU) and conciliary feedback to private practitioner

In the review of the EEG findings from the practice and the KNEU, there will be two four-fold tables (Table 5).

**Table 5 Tab5:** EEG assessments by the University Department of Neurology (KNEU) in relation to the previous assessment by the private practitioners

	Practice assessment		
Assessment KNEU	Action (2B, 2C)	No action(2A)	Total
Conventional practice EEG			
Action (1B, 1C)	a	b	a + b
No action (1A)	c	d	c + d
Total	a + c	b + d	a + b + c + d
Portable EEG			
Action (1B, 1C)	a	b	a + b
No action (1A)	c	d	c + d
Total	a + c	b + d	a + b + c + d

The first result criterion will be the proportion and the direction of the cases with discordant disposition of the two EEGs by the private practitioner (Table 3). The second criterion will be the proportion and direction of discordant results in the treatment regimen by specialists of KNEU within the framework of the pseudonymized second assessment.

In this way, it will be possible to determine how the KNEU physicians assess the portable EEG differently from the private practitioners in addition to generating insights into how these two physician groups differ from each other in terms of their assessments of the office-based EEG. Furthermore, it will be possible to observe how the assessments of the consulting physicians from KNEU differ from each other. These assessments will each be quantified as kappa values.

As a third result criterion and final evaluation level of method comparison, the original four-fold table will be prepared again after the consolidation of the first and second assessments (Table 6):

**Table 6 Tab6:** Consolidated EEG assessments jointly by the University Department of Neurology and by the private practitioners

Practice-EEG^a^	Portable EEG^b^		Total
	Action (2B, 2C)	No action(2A)	
Action (1B, 1C)	a	b	a + b
No action (1A)	c	d	c + d
Total	a + c	b + d	a + b + c + d

^a^
http://powerandsamplesize.com/Calculators/Compare-Paired-Proportions/McNemar-Z-test-2-Sided-Equality

^b^After consolidation of the initial assessment in practice and the second assessment in the University Department of Neurology

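### In the feasibility phase the practitioner can code the conventional EEG after seeing the portable one. This code feeds the first result criterion, and the protocol contradicts itself on blinding.

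*Protocol article*

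**What the plan says.** All references are to the protocol article.

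- **Order of reading** (*Indication, implementation, and evaluation of EEGs*). For the feasibility phase: "The patients will return with the headset and activity and evaluation sheet, which they will be required to complete". The next sentence, placed after that return and covering both phases, says that "the private practitioner will examine both EEGs using the same standardized assessment sheet". No step records the Table 1 code (1A, 1B or 1C) before this point. The only entry made earlier, before the conventional EEG, covers the diagnostic question, the therapeutic options and the medical history.
- **Before and after** (*Objectives*). For the feasibility phase, "we will analyze the before and after documented diagnostic findings" of the practitioners. The text does not say before and after what.
- **Blinding.** *Data analysis and measures* says that "all three assessors will document their medical reports for each blinded EEG record", and it carries the same approach into the feasibility phase. But *Indication, implementation, and evaluation of EEGs* places blinding after the practitioner's results have been collected: "In the run-up to the second assessment of both EEGs, the Data Trustee will transfer the data".
- **Independence** (*Data analysis and measures*, after Table 4). Of the practitioners: "Since they know both findings and the patient, their two EEG assessments are not independent of each other".
- **Role of the comparison** (*Randomized second assessment by KNEU*, after Table 5). "The first result criterion will be the proportion and the direction of the cases with discordant disposition of the two EEGs by the private practitioner", that is, Table 3. The pseudonymized university (KNEU) assessment is the second criterion and the consolidated Table 6 the third.
- **Test** (*Sample size calculation, Feasibility study phase*). A McNemar test is sized for discordant proportions of 0.10 and 0.05 (468 patients) or 0.13 and 0.07 (433 patients), with 500 planned. The table it applies to is not named.

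**The concern.** Table 3 is meant to show how often the portable EEG leads to a different disposition from the conventional EEG. For that, the conventional code has to record what the practitioner would have done without the portable recording. If the code can be entered or revised once the portable record is known, two things can happen. The practitioner may bring the codes into line, so that real discordances disappear. Or the conventional code may be set lower or higher in the light of the portable finding, which tilts the balance between cells b and c. McNemar's test corrects neither.

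The same codes are the practice side of Table 5 and enter the consolidated Table 6, so the problem spreads beyond Table 3. The results are intended to decide whether full-scale trials are justified, and a shrunken or tilted Table 3 could mislead that decision in either direction.

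**Working it through.** **1. The passages side by side.** The practitioner's results are collected first, and the Data Trustee blinds the records afterwards, for the two KNEU readers. The practitioner knows both findings and the patient. The statement that all three assessors report on blinded records therefore cannot hold for the practitioner. On timing, the text places the examination of both EEGs after the return of the headset. The before-and-after wording in *Objectives* points the other way but describes no lock.

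**2. The plan's own sample size.** Inputs: discordant proportions from *Sample size calculation*, two-sided alpha 0.05 (the Table 6 footnote links to a two-sided McNemar calculator), power 0.80. With pd the sum and d the difference of the discordant proportions:

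n = [1.960·√pd + 0.8416·√(pd − d²)]² / d²

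- 0.10 vs 0.05: pd = 0.15, d = 0.05; (0.7591 + 0.3232)² / 0.0025 = 468.6 (stated: 468).
- 0.13 vs 0.07: pd = 0.20, d = 0.06; 433.7 (stated: 433).

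The figures reproduce apart from rounding down. The sample size is right for its inputs.

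**3. Power at 500.** Power = Φ[(d√n − 1.960√pd) / √(pd − d²)]. For 0.10 vs 0.05: (1.1180 − 0.7591) / 0.3841 = 0.93, so 82.5%.

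**4. Shrinkage (assumed).** A share k of discordances in both directions becomes agreement.

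| k | Proportions | Power at 500 | n for 80% power |
|---|---|---|---|
| 0 | 0.10 / 0.05 | 82.5% | 469 |
| 10% | 0.09 / 0.045 | 78.4% | 521 |
| 20% | 0.08 / 0.04 | 73.4% | 587 |
| 30% | 0.07 / 0.035 | 67.7% | 671 |

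**5. Tilt (assumed).** There is no true difference (0.075 vs 0.075), and the codes shift to a net imbalance. The rejection rate adds both tails.

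- 0.085 vs 0.065: d = 0.02; upper tail Φ[(0.4472 − 0.7591) / 0.3868] = Φ(−0.81); about 21%.
- 0.09 vs 0.06: d = 0.03; Φ[(0.6708 − 0.7591) / 0.3861] = Φ(−0.23); about 41%.

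A single changed code cannot move a patient from b to c, because that needs both codes reversed. The net tilt can still arise from single changes. If the conventional code is lowered from action to no action, a patient in b moves to d and a patient in a moves to c. The first case needs 1% of patients to make each move, and the second 1.5%.

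**The case against.** The protocol does not hide the dependence. It states it, and its next sentence brings in the second opinion for the method comparison. Two independent experts then read pseudonymized, randomly divided records, and this is a criterion in its own right. That stands as mitigation, but it leaves the first criterion as it is. The joint KNEU decision on discordances also follows re-identification, so only the individual KNEU readings are clearly blinded.

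The conventional EEG is probably looked at early. The feasibility phase begins with it, and patients who need treatment after the first EEG for hazard prevention are excluded. This implies a look, not a recorded code. It also shows that entering the code at that moment is practicable. The article is condensed, and the full protocol may fix the order; but the order printed here is the wrong way round for Table 3.

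Part of the dependence is intended. Change of management is the treating physician's decision given the extra recording, and Table 4 can be coded only by someone who knows the conventional disposition. This stands: the defect is that the portable record may influence the conventional code, not that the conventional result is known when the portable EEG is coded.

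A reader might infer that the McNemar test is invalid because the pairs are dependent. It is not: the test is made for correlated pairs. A reader might also take Table 3 to be the primary endpoint and the power loss to be a fact. The criteria are numbered but none is called primary, and the McNemar test is tied to no table.

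**Conclusion.** The point holds in a limited form. As written, the conventional code in the feasibility phase can be set with the portable record already seen. That code feeds the first result criterion and Tables 5 and 6. The statement that all three assessors read blinded records contradicts two other places in the protocol.

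The size is unknown. The power figures (82.5% falling to between 78.4% and 67.7%) and the rejection rates (about 21% and 41% instead of 5%) rest on assumed contamination and on Table 3 being the table tested. They show that modest carry-over would matter, not that it will occur. The documents do not support the stronger conclusions that the sample size is wrong or that the practitioner comparison should be dropped. The issue deserves correction because the remedy is nearly free.

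**What to change.** 1. In the feasibility phase, have the Table 1 code (1A to 1C) entered, dated and locked before the portable recording is available to the practitioner. The pilot has no such code; there, have the conventional-EEG report completed before the portable record is opened.
2. In *Data analysis and measures*, state that only the two KNEU assessors read blinded records, and bring the before-and-after wording in *Objectives* into line with step 1.
3. In *Sample size calculation*, name the table to which the sized McNemar test applies. If a KNEU table is chosen, use the individual readings made before re-identification and say how the two readers' codes enter the test.

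The cost is one dated entry per patient on the existing sheet, plus wording. The lock stops the portable record from changing the conventional code. It does not make the portable reading independent, so that limitation should still be reported. Moving the sized test to KNEU would take it away from the treating physician's real decision; that trade-off is for the sponsor, and steps 1 and 2 are worthwhile whichever table is chosen.
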